## Methods

### Study design and procedure

The study is a single-blind, pragmatic, pilot randomized controlled trial with two parallel groups. According to the PRECIS-2’s domains, the study is considered rather pragmatic because of the following characteristics [24]. People with moderate to severe aphasia usually receive speech-language therapy as part of usual care in in-patient settings in China. The participants of the study will be recruited from the study site from in-patient patients. When patients with aphasia are admitted in hospitals, they usually receive speech-language therapy daily for at least 2 weeks. The study design is based on the usual SLT schedule and extended the duration per treatment session for adding the AAC intervention in usual care. The primary outcome and analysis of the study is the improvement of functional communication which is also the essential outcome in the usual care.

Participants will participate in a 1-h treatment session/day for ten consecutive days. During each session, participants will receive 30 min of AACT in addition to 30 min of SLT (experimental group) or 60 min of SLT (control group). Participants in the AACT + SLT group will learn to use a paper-made communication board to express their needs. The communication board includes 45 pictures relating to basic needs, emotional expression, medical conditions, and daily activities. Participants’ regular rehabilitation interventions, such as physical and occupational therapies, remain the same during the experimental period.

The participants will be evaluated at pre-intervention (prior to randomization) for collecting the demographic and baseline data. The post-intervention evaluation will be completed after participants complete the 10-day training, which is 2 weeks after randomization. Last, a 2-week follow-up will be conducted after the post-intervention evaluation (see Fig. 1).

**Fig. 1 Fig1:**
[figure not shown]
Flow diagram trial design

### Ethics approval

This study has been approved by the Medical Ethics Committee (MEC) of YY hospital (reference number: 2019-118, approval received in November 2019). The researchers will report serious adverse events to the MEC. The events will be managed based on institutional policies.

Any modifications to the protocol which may impact on the conduct of the study, potential benefit of the patient, including changes of study objectives, study design, patient population, sample sizes, study procedures, or significant administrative aspects, will require a formal amendment to the protocol. The PI will first notify the IRB board of the YY hospital if there is any modification needed. Such amendment will be agreed upon by the research administration center of YY hospital and approved by the Ethics Committee of YY hospital prior to implementation and notified to Shanghai University of Traditional Chinese Medicine in accordance with local regulations. Revised protocol will also be updated in the Chinese Clinical Trial Registry database (ChiCTR) as ChiCTR2000028870.

### Participants

People with aphasia who are receiving in-patient stroke rehabilitation services in Yueyang Hospital of Integrated Traditional Chinese and Western Medicine Shanghai University of Traditional Chinese Medicine, Shanghai, China (YY hospital), are screened for eligibility. The physician in the in-patient department who is in charge of the patients’ rehabilitation service will recruit the patient and provide written information and oral explanation to the participants and their family members. The SLP who is in charge of evaluation assists the physician for diagnosing aphasia and the severity of oral production. Participants are enrolled by the physician according to the inclusion and exclusion criteria as listed in Table 1. All participants and their family members are required to review the information and sign the consent form before participating in the study.

**Table 1 Tab1:** Inclusion and exclusion criteria

**Inclusion criteria** 1. Diagnosis of aphasia, after stroke, as confirmed by a qualified speech-language therapist ascertained with the Chinese Standard Aphasia Battery (ABC) test [25] 2. Moderate to severe information reduction of verbal production (percentile score of 50 or lower on the ABC verbal production subtest) 3. First onset of stroke, anytime post-stroke 4. Age 20–80 years 5. Mandarin Chinese as the first language 6. Able to participate in intensive therapy **Exclusion criteria** 1. Acute stroke with unstable vital signs 2. Premorbid speech and language disorders caused by a neurological deficit other than stroke 3. Premorbid cognitive impairment, mood disorders, and mental disorders affecting communication 4. Severe non-linguistic cognitive disturbances impeding language therapy 5. Presence of serious heart, liver, kidney, infectious disease, and uncontrolled medical problems 6. Concomitant neurological diseases other than stroke	

Once a participant is enrolled or randomized, the study site will make every reasonable effort to follow the participant for the entire study period. The research team are responsible for implementing standard operating procedures to maintain interest in the study and achieve follow-up, including regular reminders for participants and their caregivers. Since the study is conducted in an in-patient setting, the research team anticipate the retention will be good except that participants have urgent medical conditions occurring during the treatment period. Participants may withdraw from the study for any reason at any time. The investigator also may withdraw participants from the study if they are unwilling to comply with required study procedures after consultation with the Protocol Chair in YY hospital.

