**Discussion:**

This pilot RCT will contribute to new scientific evidence to the field of aphasia rehabilitation in early recovery during the in-patient period. The paper describes the trial, which will explore the effect of combining AACT and SLT and SLT only, our choice of primary and secondary outcome measures, and proposed analyses. The study results will provide information for implementing AACT in the regular in-patient SLT of future RCTs.

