It is also important to note that there is limited evidence of AACT for Chinese-speaking people with aphasia. People with aphasia in in-patient rehabilitation settings in China are mainly in acute rehabilitation or subacute facilities. Their communication demands include expressing basic and medical needs (e.g., asking a nurse to call a family member). They need to share information and feelings with their family members and interact with medical professionals about needs and concerns with regard to their healthcare. Evidence indicated that this population could learn to use yes/no cards and communication boards with pictures and words for different communication needs [12]. While the previous studies supported the concept of using AAC in hospital settings [8, 11], there is still no evidence to support this approach in Chinese-speaking people with aphasia. Therefore, an AACT RCT study is needed to investigate the feasibility of the AACT and build up the foundation of research evidence in Chinese communities.

In addition, previous studies have reported that people with aphasia and their families often reject to adopt AAC strategies with the fear that AAC may interfere with or impede the restoration of their natural language system [14, 19, 23]. Similar concerns are commonly raised in the clinical settings in China. However, studies have shown that AACT may simultaneously strengthen communication by reducing the pressure to retrieve target concepts using impaired language functions [20]. Since the present study aims to introduce a new approach (AACT) in an in-patient rehabilitation setting, considering the potential concern of people with aphasia and their families becomes essential. Therefore, instead of comparing AACT and SLT exclusively, the present study aims to compare AACT’s effect along with regular SLT to SLT only in individuals with post-stroke moderate to severe aphasia in an in-patient rehabilitation program.

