### Data analysis

Outcomes of interest will be analyzed on an intention-to-treat basis. Characteristics of the sample and the descriptive statistics will be reported. The primary analysis will be conducted without adjustment. The mixed model analysis will be used to analyze the continuous repeated-measure data because of its advantages of accommodating missing data and the flexibility in small samples and treating time. Data will be examined for differences between groups and over time. Post hoc tests will be performed to explore factors including age, sex, education, and initial stroke/aphasia severity, considered to affect the trial’s outcome. The data from conversation samples and the satisfaction survey will be suitably coded for qualitative responses to be categorized and examined.

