Our trial trains people with aphasia to use a paper-based communication board with caregivers and healthcare providers in in-patient rehabilitation settings. It is easy to access and cost-effective, which is essential for all clinical settings. As an in-patient stay is often the first step on a long-term care continuum, AAC can maximize people’s communication skills with aphasia within desired life roles and prepare them and their families for life after the in-patient stay [8]. When the trial is completed, the results will also give us a better understanding of the AACT’s dual role in simultaneously driving inter-systemic reorganization with the potential to support language function while providing compensatory strategies during communication breakdowns in in-patient settings.

In our previous experience, AAC is often not prescribed in the early stages of recovery because patients with aphasia and their family members are worried that receiving AACT will impede language recovery [19]. It is a common AAC myth in clinical settings. However, recent evidence suggests that early AACT in in-patient settings may increase AAC acceptance and decrease the risk of not using language during the early recovery stage. Early AACT may also increase people with aphasia’s motivation to communicate in various situations and have better long-term participation outcomes. Therefore, they were more active when making their healthcare decisions, experiencing increased participation in life events, and discovering new social roles [19]. This evidence supports the purpose of the trial’s intention to investigate early AACT’s effectiveness in in-patient settings. The results of the trial will also contribute to the research evidence of AACT in Chinese-speaking people with aphasia.

A limitation of this study is that this protocol is not double-blind. However, the participants and the SLP will be blinded to treatment allocation. The study also cannot eliminate the confounding effects from the early-stage spontaneous recovery after stroke. The trial is designed to investigate the effectiveness of the current practice protocol in the local site. Therefore, the follow-up is short. Since the research evidence of the effectiveness of AACT in in-patient settings is limited, the trial’s results will also provide new insight into implementing AACT in actual clinical practice.

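### The primary analysis is fixed as unadjusted in a sample open to any time since stroke; pre-specifying baseline scores and time since onset would gain modest precision, and early-recovery conclusions need limiting

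*Protocol article*

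**What the plan says.** **Who enters.** Table 1 (Participants) lists "First onset of stroke, anytime post-stroke" as an inclusion criterion. The only exclusion tied to the timing of the stroke is "Acute stroke with unstable vital signs". No upper limit on time since onset is set.

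**What the results are said to inform.** The abstract's Discussion states: "This pilot RCT will contribute to new scientific evidence to the field of aphasia rehabilitation in early recovery during the in-patient period". The main Discussion gives the trial's intention as to "investigate early AACT’s effectiveness in in-patient settings". The Objective section asks about moderate to severe aphasia in in-patient rehabilitation and does not mention early recovery.

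**How the data are analysed.** The Data analysis section says that the primary analysis makes no adjustment and that a mixed model will be used for the repeated measures. It adds: "Post hoc tests will be performed to explore factors including age, sex, education, and initial stroke/aphasia severity". Randomization and blinding describes a 1:1 list and names no stratification factor.

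**What is conceded.** The main Discussion says: "The study also cannot eliminate the confounding effects from the early-stage spontaneous recovery after stroke".

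**The concern.** The authors themselves name spontaneous recovery as a process that affects outcome, and its pace depends on how long ago the stroke occurred. Eligibility lets that interval vary without an upper limit. The stated primary method then makes no use of it, or of the baseline language score that is collected anyway.

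Two things are at stake. The first is efficiency: in a trial of 44 evaluable patients, prognostic information that is free to use is left in the residual, and a chance difference between arms in time since onset is left uncorrected in the point estimate. The second is interpretation: if a material share of patients turn out to be long past their stroke, the result does not speak to early recovery in the way that the abstract and Discussion say it will.

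**Working it through.** **Inputs from the protocol (Sample size).** Difference 1 point on CBN, SD 1, significance level 5% (two-sided assumed), power 90%, 22 per group, 20% dropout, 56 recruited.

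**Input assumed.** The share R² of remaining outcome variance explained by the added covariates is set at 10%, 20% and 30%. The protocol gives no figure. SD 1 is taken as the SD before these covariates are used.

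**Step 1: reproduce the plan.** n per group = 2(1.960 + 1.282)² × 1²/1² = 21.01, rounded up to 22. The t-test version gives 22.02, and power at 22 per group is 0.900. With dropout, 22/0.8 = 27.5, so 28 per arm and 56 in total. The stated figures hold.

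**Step 2: effect of adjustment at the planned difference.** Residual SD = √(1 − R²); SE of the difference = residual SD × √(2/22); equivalent sample factor = 1/(1 − R²). Power is from the two-sided t-test.

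| R² (assumed) | Residual SD | SE | Power at 1 point | Sample factor |
|---|---|---|---|---|
| 0 | 1.000 | 0.302 | 0.900 | 1.00 |
| 10% | 0.949 | 0.286 | 0.927 | 1.11 |
| 20% | 0.894 | 0.270 | 0.952 | 1.25 |
| 30% | 0.837 | 0.252 | 0.972 | 1.43 |

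**Step 3: what adjustment costs if the covariates explain nothing.** Three covariates reduce the degrees of freedom from 42 to 39. Power at 1 point is then 0.899 instead of 0.900.

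**Step 4: chance imbalance with 22 per arm.** For a difference of at least 0.5 SD in time since onset, z = 0.5/√(2/22) = 1.658, so the two-sided probability is 0.097. If half the patients are early, the chance that the arms differ by at least 20 percentage points in that share is 0.174; if 30% are early it is 0.137 (exact binomial, simple randomisation assumed).

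**Step 5: what such an imbalance would do.** If time since onset alone explained 10–30% of CBN variance (assumption), a 0.5 SD imbalance would move the unadjusted difference by 0.5 × √0.10 = 0.16 to 0.5 × √0.30 = 0.27 points, against a target of 1 point. This describes one unlucky allocation. Over repeated randomisations the average shift is zero.

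**Step 6: a subgroup test as an alternative.** With four equal cells of 11 and SD 1 (assumption), the SE of a treatment-by-time interaction is √(4/11) = 0.603. Power for a full 1-point interaction is about Φ(1/0.603 − 1.96) = Φ(−0.30) = 0.38.

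**The case against.** **Validity.** A reader might infer that the open time window biases the treatment comparison. It does not. Randomisation balances time since onset in expectation, and the type I error rate and confidence interval of the unadjusted analysis already allow for chance imbalance. Choosing no adjustment is legitimate. This stands in full and confines the point to precision.

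**A contradiction with the stated question.** It is tempting to say that eligibility contradicts the trial's question. The Objective does not mention early recovery. That framing appears in the abstract and main Discussion, and the Background notes that "People with aphasia in in-patient rehabilitation settings in China are mainly in acute rehabilitation or subacute facilities", which probably narrows the range in practice. Broad entry also suits a trial described as pragmatic. What remains is a mismatch of wording: the setting is not an entry limit, so the early-recovery claim depends on who is actually recruited.

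**The factor list.** One might call the absence of time since stroke from the post hoc list an error. The list is introduced as non-exhaustive, and a fuller document could add the variable. Only the positive commitment to an unadjusted primary analysis can be criticised.

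**Size.** Nothing in the protocol shows that time since stroke is a main source of variation, and the 10–30% range pools it with baseline severity. The planned mixed model may already use baseline CBN if that enters as a repeated measure. A larger gain can be displayed at a 0.75-point difference (power 0.68 rising to 0.73–0.83), but the protocol plans for 1 point and never mentions 0.75.

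**The conceded limitation.** The Discussion's caution might be read as simply wrong. It is right for change within a group, which the Objective's secondary aim and the over-time comparison in Data analysis both touch. It is too broad only for the comparison between arms.

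**Conclusion.** The point holds as an inexpensive improvement to a stated method and a limit on interpretation. It is not a flaw that invalidates the trial. The unadjusted primary comparison is unbiased in expectation; it forgoes precision and leaves the estimate exposed to chance imbalance at about 22 per arm.

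At the planned 1-point difference, power would rise from 0.90 to 0.93–0.97, equal to 11–43% more patients. This depends on the covariates explaining 10–30% of remaining variance, on SD 1 being the SD before they are used, and on 22 evaluable patients per arm. If they explain little, the gain is close to nil, but so is the loss. Confidence in the direction is high; confidence in the size is low, because the documents supply no variance share.

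The early-recovery wording cannot be judged until the distribution of time since stroke is known.

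**What to change.** Before any unblinded analysis:

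1. Replace the unadjusted primary model with one that pre-specifies baseline CBN (as a covariate or through the repeated-measures structure), baseline ABC and log time since stroke onset. Keep the unadjusted result as a sensitivity analysis.
2. Report time since stroke by arm, and limit statements about early recovery to what that distribution supports.
3. In the Discussion, clarify that spontaneous recovery confounds change within a group, while the randomised comparison between arms controls for it in expectation.

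Do not put a treatment-by-time-since-stroke interaction test in place of the listed exploratory factors; at this size it would be too weak to inform (power about 0.38 for a full 1-point interaction).

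The cost is a dated change to the analysis plan and some rewording. Baseline CBN and ABC are already collected, and the onset date should be in the in-patient record (assumption). Eligibility and sample size stay as they are. According to Trial status, 14 participants had been randomised at publication, so the change could still be made well before analysis.

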### Randomization and blinding

In-patient participants in YY hospital who meet the inclusion criteria will be randomly assigned to the experimental or control groups after the pre-intervention assessment. A researcher who is not involved in the study will generate a randomization sequence list based on the ratio of 1 to 1 for two groups. Group allocation will be obtained at the beginning of the first intervention session. The SLP in charge of all intervention sessions will open an opaque envelope that includes the assigned allocation. Another SLP who does not know the treatment allocation will conduct all the participants’ pre- and post-intervention assessments, and pre-intervention assessment will be performed before group allocation. The SLP performing the intervention is not blinded to group allocation because of the nature of the intervention, while the participants are blinded to allocation since they only know that the intervention is to help them improve communication, and can hardly distinguish AAC from SLT. Data analysis will be conducted by a data analyst who is blinded to group allocation.

### Intervention

#### Control group (SLT only)

The participants in the SLT only group will receive a 1-h regular SLT per day for ten sessions. Fifty words related to the stroke rehabilitation program’s routine are selected. The fifty words include categories as vegetables and fruits, daily supplies, daily actions, body parts, and the salutation of surrounding medical professionals and family members (husband/wife, son/daughter, physician, nurse, caregiver). These words are presented with a picture and a written word. The 50 words are divided into five sets (10 words/set) according to categories. Participants will practice one set every 2 days.

Participants learn the semantic and phonological knowledge of 10 words and conduct auditory comprehension (selecting target word from two/four words following verbal directions from the SLP), word repetition, and naming tasks of learned words in each session. The tasks and training procedures are the same in each session. The procedures are as follows: (1) participants are taught with the semantic and phonological knowledge of the target word one by one; (2) they are asked to repeat the word with the SLP; (3) they are asked to do auditory comprehension tasks by selecting target words from two or four cards; and (4) they are asked to name the target picture based on the Cueing Hierarchy [26].

#### Experimental group (AACT + SLT)

The experimental group will receive AACT (0.5 h) + SLT (0.5 h) per session. Participants will learn how to point to the target icons on a paper-based communication board to answer questions (e.g., “Do you have pain?”, “Where is your pain?”) in line with studies that apply AACT for people with aphasia [8, 12, 27]. The communication board contains 45 icons designed for people with aphasia to communicate with medical professionals and family members in the in-patient setting. These icons are pictures of everyday needs, clinical symptoms, types of medical care, rehabilitation services, names of people around, yes/no signs, and a rating scale, with Chinese written words on the top of each icon.

Each intervention includes three training tasks. These tasks aim to help people with aphasia learn how to use the communication board [21]. The first task is symbol identification. Participants are asked to identify each icon on the communication board following verbal directions from the SLP. At first, the SLP presents the verbal model plus a demonstration: the SLP saying “point to [target icon]” while physically modeling the desired response by pointing to the target icon on the communication board. After the modeling, participants are asked to follow the exact directions. Next, the SLP presents a verbal cue only: the SLP saying “point to [target icon],” and then requires the participant to point to the target icon independently. The second task is to answer yes/no questions. The SLP asks a yes/no question relative to a particular icon (is this a picture of [target icon]) and then asks the participant to respond to the question by pointing to the yes or no icon on the communication board. The third task is to respond to questions with a specific icon. The SLP asks an open-ended question relative to a particular icon (e.g., “if you have a headache, which icon will be selected to tell the people who are surrounding you?”). Then the participant responds to the question by pointing to the target icon.

